### Biopsychosocial model of chronic pain

The conceptual model for the present study is built within the biopsychosocial model of chronic pain [57]. The frequent co-occurrence of affective disorders, other functional GI disorders, and non-GI complaints suggests that the maintenance and treatment of IBS can best be understood using a biopsychosocial model [16]. It is likely that biological factors such as genetics and visceral hypersensitivity along with psychological and lifestyle factors all contribute towards IBS-related pain and functioning. Twin studies have shown that while genetics play an important role in IBS symptoms, environmental factors such as social learning contribute an equal or even greater etiological influence [58]. Thus, an integrative treatment strategy for patients with IBS is warranted. IY represents a non-pharmacological intervention that can be integrated into a conventional treatment plan. Within the conceptual model below, IY is viewed as impacting IBS symptoms and pain through physical, psychological, and spiritual mediators. Such examination of mediators has been deemed critical, both for understanding treatment components as well as to further our knowledge of functional disorders [59]. Derived from the biopsychosocial model of pain and yoga philosophy, Figure 1 depicts a conceptual model of how IY may improve IBS pain, functioning, and stress. The model offers a guiding heuristic for conceptualizing the benefits of IY for IBS; the model does not depict all possible pathways across domains. The outcomes in the model represent the study's primary outcomes, and the physiological, psychological, and spiritual mechanisms represent the exploratory mediators to be tested.

### Physiological mechanisms

It is thought that yoga quiets the body as well as the mind through attention and vascular and muscular relaxation [60]. Yoga has been associated with a number of physiological benefits. Research linking yoga with ANS functioning has found improved physiologic responses, including reduced diastolic and systolic blood pressure, decreased heart rate, and increased heart rate variability, indicative of healthy functioning [61-64]. IY appears to be especially involved in enhancement of cardiac parasympathetic system modulation, consistent with a reduction in stress response pathophysiology [64]. It is possible that breath awareness during yoga produces a high level of autonomic control. For example, after a month of yoga practice, a group of 12 healthy participants had a lower resting heart rate after the intervention compared to a group of 12 controls; individuals in the yoga group were also able to significantly lower their heart rates when given instruction to do so [65]. It is unknown whether similar autonomic enhancement will be evident in young IBS patients; however, biofeedback, which incorporates autonomic control, has been used successfully with children as young as 8 years of age [66]. Yoga may also impact the endocrine system and HPA reactivity. It is believed that *asana *practice massages the internal organs, resulting in enhanced blood circulation, glandular functioning, and ultimately balancing of hormone production [60]. A number of studies have found changes in cortisol, a measure of stress response system activation, following yoga [67-69]. The physiological benefits of yoga may prove beneficial to many IBS patients, particularly those with ANS and HPA axis dysregulation. Accordingly, cortisol, ANS arousal, and visceral sensitivity will be measured before and after the intervention and compared to the standard care controls.

### Psychological mechanisms

Yoga has a number of positive effects on psychological functioning that have been reported in healthy, pain, and stress groups and for a wide variety of age groups. Two recent reviews examining yoga for depression and anxiety underscored the promise of yoga for elevating mood. Out of five RCTs of yoga for depression, beneficial effects were reported in four [49]. All eight randomized studies of yoga for clinical anxiety disorders reported a reduction in symptoms following yoga [50]. For example, Woolery et al. [67] reported reduced depression and anxiety after a 5-week IYP in depressed young adults. Similarly, Shapiro [70] found that a 20-week IYP led to reductions in depression, anger, anxiety, and neurotic symptoms in 17 patients with major depression (aged 20-71 years). Other positive psychological effects include coping and self-efficacy. Adolescents with IBS were found to have reduced anxiety and less emotion-focused coping following four weeks of home-practice yoga [51]. Persisting in a yoga class promotes a sense of accomplishment that is consistent with the development of self-efficacy. Given the previous role of competence in the link between adolescent IBS patients' symptoms and disability [15], it is likely that a sense of mastery achieved through yoga will positively impact symptoms. Self-efficacy, effective coping, and positive psychological functioning, in turn, are related to better physical functioning in patients experiencing chronic pain and illness [71]. Thus, it is anticipated that yoga will enhance patients' coping, psychological functioning, and self-efficacy, all of which are expected to mediate the hypothesized improvement in clinical symptoms following the IYP.

### Spiritual mechanisms

Related to the psychological benefits of yoga are the spiritual underpinnings of yoga. Spirituality and well-being appear to be connected, particularly in those experiencing chronic illnesses [72]. Two aspects of spirituality that IY is likely to impact are mindfulness and acceptance, both of which will be tested as mediators in the present study. IY is associated with a mastery of life challenges, which may extend to dealing with chronic illness and pain [73]. As noted by BKS Iyengar, "The pain is there as a teacher... We must try not to run from pain but to move through it and beyond it" [74]. It is anticipated that the IYP will enhance patients' compassionate understanding, an Eastern concept that in this context can be conceptualized as compassion towards oneself or acceptance (i.e., acceptance of one's health condition). Such acceptance or understanding of one's state appears to be important for those with chronic pain [75]. IY is also associated with mindful awareness, a concept that has been integrated in empirically-validated approaches including cognitive-behavioral therapy [76]. Mindfulness is an openness or receptive awareness to what is occurring in the present. Mindful activity has been found to improve mood and stress [77] likely through strengthening attention [60]. Use and control of attention can be turned towards minimizing stress, disability, and pain. It has been theorized that mindfulness may be especially effective in treating functional disorders such as IBS [16]. It is anticipated that IY will lead to an increase in mindfulness and acceptance which will in turn improve functioning among young IBS patients.

## Aims

The purpose of the proposal is two-fold: 1) to examine the effects of an IYP on IBS symptoms, global improvement, and quality of life in adolescents and young adults aged 14-26; and 2) to explore the mediating roles of physiological and psychospiritual processes through which IY is likely to impact outcomes.

The specific aims of the proposed project are:

1. To determine the safety, feasibility, and acceptability of the IYP in IBS patients aged 14-26 years.

2. To test for changes in clinical symptoms (primary outcomes), including self-reported IBS symptoms, global improvement, and health-related quality of life (HRQOL) immediately following a standardized IYP and at 2-month follow-up compared to usual care wait-list controls.

3. To assess changes in visceral sensitivity (assessed via a standardized laboratory visceral sensitivity task), disability and psychospiritual functioning (i.e., catastrophizing, mood, self-efficacy, acceptance, and mindfulness) (secondary outcomes) following the IYP compared to controls.

4. To explore potential mediators of clinical outcomes following the IYP, including psychospiritual functioning, visceral sensitivity, and ANS and HPA activity.

The hypotheses to be tested are:

1. The IYP will be safe, acceptable and feasible: at least 80% of subjects will complete the IYP.

2. Following the IYP, participants will demonstrate significantly greater improvement on the primary clinical outcomes of IBS symptoms, global improvement, and HRQOL relative to wait-list controls; gains will also be evident at the 2-month follow-up.

3. Following the IYP, participants will demonstrate significantly reduced visceral sensitivity and disability, and improved psychospiritual functioning, including coping, mood, self-efficacy, acceptance, and mindfulness (secondary outcomes) relative to wait-list controls.

4. Exploratory hypothesis: The impact of the IYP on the primary clinical outcomes will be mediated by improved psychospiritual functioning, reduced visceral sensitivity, and improvements in ANS and HPA dysregulation.

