**Methods/Design:**

Sixty irritable bowel syndrome patients aged 14-26 will be randomly assigned to a standardized 6-week twice weekly Iyengar yoga group-based program or a wait-list usual care control group. The groups will be compared on the primary clinical outcomes of irritable bowel syndrome symptoms, quality of life and global improvement at post-treatment and 2-month follow-up. Secondary outcomes will include visceral pain sensitivity assessed with a standardized laboratory task (water load task), functional disability and psychospiritual variables including catastrophizing, self-efficacy, mood, acceptance and mindfulness. Mechanisms of action involved in the proposed beneficial effects of yoga upon clinical outcomes will be explored, and include the mediating effects of visceral sensitivity, increased psychospiritual resources, regulated autonomic nervous system responses and regulated hormonal stress response assessed via salivary cortisol.

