The present study will address a number of the limitations of previous studies. Primarily, the current sample will be sufficiently large to detect treatment effects (see Power analyses below) and will involve an RCT with an appropriate control group for this stage of the clinical trial process. The selection of a wait-list control condition was based upon consideration of the literature and a lack of consensus regarding an acceptable attention control condition to compare to yoga. In this preliminary study, the control group will involve patients receiving care as usual for the length of the yoga intervention. Symptoms, physical activity, and lifestyle changes will be assessed weekly in both the yoga and control groups. While the control group will not account for the social, attention, or expectation aspects of the IYP, a usual care control group is appropriate at this stage of the research when examining a novel treatment in an untested population. If the IYP is found to be superior to the wait-list group in this exploratory study, a future R01 will incorporate a control condition that accounts for the social, attention, and expectation effects of a group-based intervention.

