Those initially assigned to IY will then engage in the 6-week biweekly program (each session will last 1.5 hours; total duration = 18 hours), while those assigned to the control group will receive care as usual. All participants will repeat the baseline assessments, including the sensitivity task and psychophysiological assessment and cortisol collection, immediately following the total treatment/control period. Questionnaires regarding symptoms will also be e-mailed at a 2-month post-treatment follow-up. Both the yoga and control groups will receive a weekly monitoring form to assess symptoms, physical activity, and lifestyle changes (and to ensure that the control group does not participate in any mind/body interventions that may impact findings). The weekly monitoring form will be administered by phone or e-mail to both groups at the end of each week. After the 6 weeks, controls will be re-assessed to ensure that they still meet study eligibility criteria; those who continue to meet criteria will take part in the IYP. Following IY, participants will repeat the baseline assessments at post-treatment and complete the 2-month post-treatment follow-up questionnaires.

According to the Power/Sample Size calculations outlined below, 30 patients in each of the intervention and control groups will be recruited (total n = 60). To accommodate this number, 4 IY groups and 4 initial control groups will be conducted, with approximately 8 patients per group.

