To test **Hypothesis 2: **Participants in the IY group will demonstrate significantly greater improvement in IBS symptoms, global improvement and HRQOL apparent immediately post-intervention and at the 2- month follow-up. Consistent with recommendations regarding analyses for randomized trials, analysis of covariance (ANCOVA) will be used to test group differences [123]. The baseline scores of the outcome variables will be entered as independent variables. The Next, analyses will assess maintenance of treatment gains during the follow-up period. Changes in IBS symptoms, HRQOL and improvement across baseline, post-treatment and follow-up will be evaluated using ANCOVAS. An intent-to-treat (ITT) analysis on the primary outcome measures will be conducted to confirm findings in treatment completers by including all participants who enrolled in the study, using the last observation carry forward approach. Even if significant differences are noted, consideration will be given to established minimally clinically significant differences on outcome measures between the groups. Thus, in order to be considered a clinically meaningful difference, participants must evidence a decrease in at least 50 points on the IBS-SSS in comparison to controls.

To test **Hypothesis 3: **Participants in the IY group will report significantly reduced visceral sensitivity, disability and improved psychospiritual functioning. The same methods will be used as described above for hypothesis 2. Similar analysis will be conducted to examine changes in visceral sensitivity, disability and psychospiritual functioning, including self-efficacy, coping, mood, acceptance and mindfulness from baseline to post-treatment.

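### The planned 2-month comparison of yoga with usual-care wait-list controls has no randomised usual-care group left, because still-eligible controls receive yoga after week 6

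*Protocol article*

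**What the plan says.** Three places in the protocol article describe a between-group comparison at follow-up.

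- The abstract (Methods/Design) says the groups will be compared on symptoms, "quality of life and global improvement at post-treatment and 2-month follow-up".
- Aim 2 sets the primary outcomes "immediately following a standardized IYP and at 2-month follow-up compared to usual care wait-list controls".
- Data analyses restates Hypothesis 2 as "Participants in the IY group will demonstrate significantly greater improvement in IBS symptoms, global improvement and HRQOL apparent immediately post-intervention", and the same sentence extends this to the 2-month follow-up.

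Two places say how long usual care lasts.

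- The section Yoga as treatment for IBS says "the control group will involve patients receiving care as usual for the length of the yoga intervention".
- The Design text, printed under the Randomization subheading, says "After the 6 weeks, controls will be re-assessed to ensure that they still meet study eligibility criteria", and "those who continue to meet criteria will take part in the IYP". Post-treatment and 2-month questionnaires then follow the yoga.

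Two places allow a softer reading of the follow-up. In the Aims, the last clause of Hypothesis 2 is only that "gains will also be evident at the 2-month follow-up", with no comparator named. In Data analyses, the follow-up step is introduced as a check on whether gains are kept, and continues: "Changes in IBS symptoms, HRQOL and improvement across baseline, post-treatment and follow-up will be evaluated using ANCOVAS". Neither place says how controls who have had yoga by then are to be handled.

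**The concern.** The comparison named in Aim 2 needs a group still in usual care 2 months after the yoga arm finishes. The schedule ends usual care at week 6 for every control who still meets the criteria. After that, the label of usual care wait-list control no longer describes what most of the control arm has received.

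Two misreadings could follow. If yoga works and its effect lasts, controls who take it will catch up, and the absence of a group difference at 2 months could be taken as loss of benefit. If a difference is seen, it could reflect time since yoga, or which controls went on to take it, and not yoga against usual care. Aim 2 covers the trial's primary outcomes, so this affects a main conclusion.

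**Working it through.** **1. The plan's own sample size.** The section Sample size determination and power analysis uses a pre/post by group interaction, a medium effect, alpha 0.05, power 0.80 and correlations of 0.10 to 0.50. Taking medium as f = 0.25 (the number is not printed), with noncentrality f² × N × 2 / (1 − r), two groups and two time points:

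- r = 0.10 gives N = 60, and r = 0.50 gives N = 34, as printed.
- The middle value is (60 + 34) / 2 = 47. For 20% attrition, 47 / 0.8 = 58.75, so 59; with an even 48, 48 / 0.8 = 60, as printed.

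The figure reproduces. It rests on one pre/post contrast and does not address a between-arm contrast after controls have had yoga.

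**2. The timeline.** Inputs are a 6-week programme (Dose), a 6-week control period (Design) and follow-up 2 months after treatment (Design). Two months is taken as 8 to 8.7 weeks. Assumption: controls start yoga straight after re-assessment.

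| | Yoga arm | Controls who cross over |
|---|---|---|
| Usual care | none planned | weeks 0–6 |
| Yoga | weeks 0–6 | weeks 6–12 |
| Own 2-month follow-up | 6 + 8 to 8.7 = week 14 to 14.7 | 12 + 8 to 8.7 = week 20 to 20.7 |

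At the yoga arm's follow-up, these controls are about 14 − 12 = 2 to 14.7 − 12 = 2.7 weeks past their own yoga.

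**3. What a between-arm test at 2 months would then estimate.**

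- *Common calendar time, everyone kept in the randomised arm:* a randomised comparison of immediate with delayed yoga.
- *Each arm's own 2-month follow-up:* yoga against yoga, at different calendar times, with controls who did not cross over left out. That omission depends partly on still meeting criteria after randomisation.

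Neither is yoga against usual care.

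**4. How far the difference shrinks.** Let a share s of controls cross over and gain a fraction q of the yoga arm's effect d. The expected difference between arms as randomised is d × (1 − s × q). The following values are assumptions, since the protocol gives none: d = 0.5, baseline correlation 0.5, 47 analysed (23.5 per arm).

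- ANCOVA residual SD = √(1 − 0.5²) = 0.866.
- Standard error = 0.866 × √(2 / 23.5) = 0.253.
- Power = the chance of a significant result in favour of yoga (two-sided 0.05) = 1 − Φ(1.96 − difference / 0.253).

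| Controls crossing over (s) | Effect gained (q) | Expected difference | Power |
|---|---|---|---|
| 0% | – | 0.50 | 51% |
| 50% | half | 0.375 | 32% |
| 50% | full | 0.25 | 17% |
| 80% | half | 0.30 | 22% |
| 80% | full | 0.10 | 6% |
| 100% | half | 0.25 | 17% |
| 100% | full | 0 | 2.5% (one tail of alpha) |

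The 51% is for a single between-arm ANCOVA under these assumptions and should not be set against the plan's 0.80, which belongs to a different test. The point is the fall from the first row to the others.

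**The case against.** The case on the other side has several sound parts.

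- **Hypothesis 2 in the Aims.** Its comparator belongs to the post-treatment clause; the follow-up clause speaks only of gains. Data analyses also frames the follow-up as maintenance, and its ANCOVA sentence names no group factor. On that reading the 2-month analysis is a durability check, and it would show the yoga arm's retained gains directly. This stands, and it shows that part of the text already holds the right reading. It does not remove Aim 2, the abstract or the restated Hypothesis 2, which say something else about the same data.
- **Untreated controls.** A reader might infer that no untreated participants remain at 2 months. The documents do not support that: controls who no longer qualify are not sent into yoga. They are a selected subset, though, and cannot stand in for the randomised usual-care arm.
- **Randomisation.** A reader might infer that no randomised comparison at all is possible at 2 months. That is too strong. Arms compared as randomised at a common calendar time remain a valid contrast of immediate with delayed yoga; it answers a different question from Aim 2. Selection enters only if controls who did not cross over are dropped or each arm's own clock is used.
- **Timing and size.** The start of the controls' yoga is not printed, so the week counts are assumed. A difference of zero is a limiting case that needs complete crossover and equal effect.
- **Importance.** The protocol calls the study preliminary and exploratory, and its sample size does not rest on follow-up. This limits the damage, but a stated comparison on primary outcomes still cannot be delivered as described.

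**Conclusion.** The point holds as an internal contradiction. The abstract, Aim 2 and the restated Hypothesis 2 promise yoga against usual care at 2 months, while the design ends usual care at week 6 for controls who still qualify, and the printed analysis does not deal with the crossover. No randomised usual-care group remains for that comparison.

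The size depends on three things that the documents do not fix: how soon controls start, how many cross over, and how much they gain. Under prompt start and the illustrative values above, power drops from about 51% to between 6% and 22% when 80% cross over, and the expected difference approaches zero as crossover and response approach those of the yoga arm. It would be wrong to conclude that all of Hypothesis 2 is untestable: the post-treatment comparison at week 6 comes before any control takes yoga and is unaffected, and maintenance within participants can be described, though without a control.

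**What to change.** 1. State that the randomised test of yoga against usual care is made at the post-treatment (6-week) assessment only.
2. Reword the abstract, Aim 2 and the restated Hypothesis 2 in Data analyses so that the 2-month follow-up is described as maintenance of gains, in line with the follow-up clause of Hypothesis 2 in the Aims.
3. Analyse the 2-month data as uncontrolled within-participant change from baseline and from post-treatment, with 95% CIs, and label it as uncontrolled. If delayed starters are included, report them separately from immediate starters.
4. Do not present any between-arm contrast at 2 months as yoga versus usual care. If one is shown, call it immediate versus delayed yoga, at a common calendar time with all participants in their randomised arm.

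The cost is wording and analysis text. Visits and treatment do not change. The price is a weaker 2-month claim: it can say whether gains were kept, not that they exceed what usual care would have given.

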### Additional measures

**1**. An **expectation **question will be administered after assignment and before treatment to assess whether treatment expectation impacts outcomes. Subjects will be asked to rate on a scale of 0 to 10 'How much do you think the treatment will benefit you or improve your IBS symptoms?'

**2**. The **weekly monitoring form **will include items related to mood, IBS pain, symptoms and functioning and use of any new interventions. The form will be administered by telephone or e-mail at the end of each week to both groups. The weekly monitoring form is an important tool in the study design, given that IBS is a condition without clear biomarkers to assess illness severity and progression, self-reported pain, symptom and functioning tools will form the basis for assessment of appropriate dose. The form will also ensure the control group does not introduce any new mind-body treatments during the intervention.

**3**. Females will receive a question that asks about their last menstrual period (LMP) to control for potential varying pain sensitivity over cycle phase. Self-reported menstrual cycle length is a common, non-invasive clinical marker for reproductive function [122].

Participant Burden: It is anticipated that the laboratory procedure and the standardized questionnaires will take 1.5 hours at baseline, and 1.5 hours post-treatment. The 2-month follow-up is expected to take 40 minutes. The weekly monitoring form will take approximately 8-10 minutes each week.

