### Data analyses

Each stage of data analysis detailed below will be carried out separately for adolescent (14-18 yrs) and young adult (19-26 yrs) sub-groups. If no differences are found, the groups will be combined. It is unlikely that differences will emerge in terms of feasibility, efficacy or safety, but a separate analysis of sub-groups will ensure that findings are generalizable across the ages studied.

Once the data set has been cleaned and examined for skewness, exploratory data analyses will be conducted using univariate methods to describe the variables of interest and bivariate techniques to characterize their interrelationships within our sample. Continuous variables will be summarized over time in each group using means, medians, range, interquartile range and standard deviations. Cross tabulated frequencies will be given for all discrete variables by group and time. Both parametric and non-parametric correlations will be reported. Expectation ratings will be correlated with primary outcomes to determine whether patient expectations were related to post-intervention symptoms.

For **Hypothesis 1**: IY will be safe, acceptable and feasible: more than 80% of subjects will complete the training program, the frequencies of drop-outs for the IYP and control groups will be examined. Attrition rates will be compared between the yoga and control groups; demographics and baseline values of functioning between those who complete the protocol and those who do not will also be compared. If drop-outs are random, then the results may be considered unbiased. If drop-outs are not random, the direction and magnitude of potential biases will be considered.

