#### Safety aspects of the study design and conduct

The major potential risks from the yoga class are strains or injuries. We will minimize these risks by conducting the yoga intervention in the safest manner possible. A progressive series of poses has been developed for this trial; this gradual progression, tailored to the participants, is designed to avoid injury. In addition, props will be used to support participants in more challenging poses. The general safety parameters of the yoga program are: 1) heart rate will not exceed moderate training range (115 BPM) - we will ask participants to check their pulse at the end of each yoga session during a timed one-minute period and to report their heart rate (anyone who remains at a rate of greater than 115 BPM will be interviewed and assessed by a physician to determine if this is a consistent finding or if there may be other isolated reasons for the tachycardia, such as a viral illness); 2) attention will be paid to spinal safety; 3) balance will be carefully monitored (e.g., chairs are used to assist balance as needed). Students will be given modifications of postures using props to accommodate for individual differences and limitations and receive individual attention if postures are too challenging.

To minimize potential risks or discomfort associated with the laboratory tasks, an experimenter will remain in the room for supervision and observation of subject responses. If subjects show signs of acute distress (e.g., tearfulness), the experimenter will stop the experiment and talk with the individual until he/she feels calmed. The patient can end the study participation or continue, depending upon how he/she feels. The team has developed ways of carrying out laboratory pain research with children to minimize threat and to make it an interesting and pleasantly novel experience.

To minimize any potential risks or discomfort associated with study assessments, all assessments will be conducted in a private room. Participants will be encouraged to raise questions or concerns at any time and be reminded that they may withdraw at any time without penalty. In addition, a clinical psychologist will train all research personnel to identify and report any history of abuse or risk for potential self- or other-harm if this information is revealed in responses to questionnaires or during interviews, as required by the study institution's IRB.

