#### Content of safety reports

The following performance and safety characteristics will be tabulated monthly and reported to the safety committee bi-monthly. Information on the date, time and nature of any adverse events will be reported separately for the yoga intervention and the visceral sensitivity task.

Performance summary:

1. Recruitment rates, including number of subjects who are screened, percent eligible at each stage of screening, reasons for non-eligibility, baseline visit rates, and randomization figures

2. Demographics of screened and enrolled participants by treatment group

3. Adherence of participants to study treatment (i.e., class attendance)

4. Percent of participants evaluated at each follow-up point and reasons for losses to follow-up

Safety summary:

Iyengar yoga intervention

1. Worsening of symptoms, as documented by the weekly monitoring form

2. Possible side effects, including any cardiovascular event during class

3. Injuries occurring in class or during home practice

4. Any other unrelated, possibly related, and related adverse events by subject

5. Attribution of adverse event to the study intervention, determination of whether the adverse event was expected or unexpected, and study adjustments as necessary

Laboratory visceral sensitivity task

1. Possible side effects, including any cardiovascular event

2. New pain that persists by the end of the lab session

3. Any other unrelated, possibly related, and related adverse events by subject

4. Attribution of adverse event to the study intervention, determination of whether the adverse event was expected or unexpected, and study adjustments as necessary

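### Hypothesis 1 makes completion of the program the only stated criterion for safety, and the harms the trial collects have no stated link to the Aim 1 safety conclusion

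*Protocol article*

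**What the plan says.** The protocol article's Aims section lists as its first aim "To determine the safety, feasibility, and acceptability of the IYP in IBS patients aged 14-26 years". The matching hypothesis in the same section reads "The IYP will be safe, acceptable and feasible: at least 80% of subjects will complete the IYP". No other criterion for safety is stated there.

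The Data analyses section restates Hypothesis 1 with a slightly different threshold, "more than 80% of subjects will complete the training program", and then gives the analysis. First, "the frequencies of drop-outs for the IYP and control groups will be examined". Then, "Attrition rates will be compared between the yoga and control groups". Completers and non-completers are also compared on demographics and baseline functioning, to judge whether drop-out is random. No injury, adverse-event or symptom-worsening measure appears under Hypothesis 1.

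Elsewhere the protocol does deal with harm. The section on safety aspects of design and conduct says "The major potential risks from the yoga class are strains or injuries". The section on the content of safety reports lists, among other items, worsening of symptoms from the weekly form, "Injuries occurring in class or during home practice", possible side effects, and adverse events with attribution and expectedness. These are tabulated monthly and go to the safety committee every two months.

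**The concern.** Safety is named first in Aim 1, so the trial intends to state a conclusion about it. The stated criterion measures something else. A participant can strain a muscle and still complete all twelve classes. Another can stop for transport or timetable reasons and be unharmed. Completion responds to harm only so far as harm causes people to leave, and it responds equally to every other reason for leaving.

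Followed as written, the criterion can be met by a program that injures many participants and missed by one that injures nobody. The data needed for a proper statement are already being gathered, but they are directed only to oversight during the trial.

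**Working it through.** **Inputs from the protocol article.** 30 patients per arm (Design; sample size section). Completion threshold of 80% (Aims; Data analyses). Assumed attrition of 20% (sample size section). The article gives no injury rate and no acceptable limit for harm, so every injury figure below is an assumption for illustration.

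**1. The plan's own figure.** Take a medium effect as f = 0.25, with α = 0.05, power 0.80, and a two-group by two-time interaction with noncentrality f²·N·2/(1 − ρ). Then ρ = 0.10 gives N = 60 and ρ = 0.50 gives N = 34, as stated. The midpoint is (60 + 34)/2 = 47. Allowing for 20% attrition, 47/0.80 = 58.75, so 59, or 60 in two equal arms. The arm size of 30 reproduces. No figure in this calculation concerns safety.

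**2. What the threshold requires.** 0.80 × 30 = 24. The Aims wording (at least 80%) needs 24 completers. The Data analyses wording (more than 80%) needs 25. The two disagree at exactly 24 of 30.

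**3. What a met criterion can hide.** With 24 completers, six did not complete. If all six left injured, the proportion is 6/30 = 20%, Clopper-Pearson 95% CI 7.7% to 38.6%. The criterion places no limit on injuries among the 24 who completed.

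**4. How the criterion responds to injury.** Let q be the injury rate, s the share of injured participants who drop out, and d drop-out for other reasons. Completion probability is p = (1 − d)(1 − q·s), and the criterion is met with probability P(X ≥ 24), X ~ Binomial(30, p). With q = 30%:

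| s | d | p | P(at least 24) | P(at least 25) |
|---|---|---|---|---|
| 0 | 5% | 0.950 | 0.999 | 0.997 |
| 0 | 10% | 0.900 | 0.974 | 0.927 |
| 25% | 5% | 0.879 | 0.937 | 0.852 |
| 25% | 10% | 0.833 | 0.773 | 0.612 |
| 50% | 5% | 0.807 | 0.647 | 0.469 |
| 50% | 10% | 0.765 | 0.421 | 0.260 |

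When s = 0, q drops out of the formula, so the first two rows hold at any injury rate.

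**5. The opposite error.** For a harmless program with true completion of 70%, P(X ≥ 24) = 0.16, so it misses the criterion with probability 0.84. At the protocol's own planning value of 20% attrition (p = 0.80), the criterion is met with probability 0.61 (24 or more) or 0.43 (25 or more), whether or not anyone was hurt.

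**6. What 30 participants can show about harm.** Exact two-sided 95% intervals: 0/30 gives 0% to 11.6% (upper limit 1 − 0.025^(1/30)); 3/30 gives 2.1% to 26.5%; 9/30 gives 14.7% to 49.4%.

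**The case against.** The best defence is that Hypothesis 1 is loosely worded and the rest of the article shows what was meant. The Abstract ties attrition below 20% to feasibility alone. The Introduction and Data analyses sections name safety separately from feasibility when they describe the age sub-groups. Harms are tabulated, attributed and reviewed by a committee that can ask for unblinded information, and pulse is checked after each class. Six injury-related drop-outs would show up in those reports, and a difference in attrition would show up between arms. The layout of adverse-event tables is normally left to a fuller document.

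Much of this stands, and it rules out several stronger readings:

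- A reader might infer that adverse events are ignored. They are not; they are collected and overseen.
- A reader might infer that the weekly form misses home-practice injuries, because its description ("items related to mood, IBS pain, symptoms and functioning and use of any new interventions") names no injury item. The documents do not show that. The intervention section says home practice is monitored on that form and at follow-up, the safety reports commit to home-practice injuries, and an article may abbreviate a form.
- A reader might infer that the safety claim will drive the larger trial. The Significance section lists attrition, response rates, effect-size intervals and similar quantities as what informs later work, and does not list safety.
- The upper limit of about 12% for zero events applies to the randomised yoga arm. Controls who remain eligible take the program later. If all 30 did so, 0/60 would give 1 − 0.025^(1/60) = 6.0%, a best case without a concurrent control.

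The defence does not remove the core point. The article attaches completion to safety twice, in the hypothesis and again in its analysis. That is a stated criterion that does not measure harm, so it is more than detail deferred to another document. The sub-group sentences name no safety measure that could replace it.

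**Conclusion.** The point holds as a mismatch between an aim and its criterion. Completion is the only stated criterion for safety, its analysis uses only drop-out and attrition, and the harms listed for the safety committee have no stated link to the Aim 1 conclusion. With 24 of 30 completing, the Aims criterion is met regardless of the number injured. Under an assumed 30% injury rate, the probability of meeting it runs from 0.999 down to 0.42, depending on assumed drop-out behaviour.

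These figures assume 30 yoga participants as the denominator and independent outcomes. The injury and drop-out inputs are illustrative. The mismatch itself does not depend on any of them. It does not follow that harm would go unseen during the trial, since the safety reports would record it. The defect should be corrected because safety is part of an aim in a study that includes minors, and the correction is cheap.

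**What to change.** Limit the 80% completion criterion to feasibility and acceptability, in line with the Abstract's use of the attrition figure for feasibility. Choose one wording (at least 80% or more than 80%) and use it in both the Aims and the Data analyses sections.

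Base the safety conclusion on the data already listed for the safety reports. For all randomised participants in each arm over the same six weeks, completers or not, give numbers and proportions with exact 95% confidence intervals for injuries, any adverse event, and symptom worsening. Using all randomised participants gives both arms a defined denominator; a rule based on class attendance would leave the controls without one in that window. Add a separate, uncontrolled summary for wait-list participants who later take the program.

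Replace the assertion that the program will be safe with a descriptive statement bounded by the upper confidence limit. For example, no injuries among 30 would be reported as compatible with a true rate of up to about 11.6%.

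The cost is a reworded hypothesis, one extra table and a more modest safety claim.
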